### Anthropometric measures

At the beginning and end of each intervention period, body weight, height, and waist circumference will be assessed, and BMI will be calculated.

### Blood pressure

Systolic and diastolic blood pressure of each volunteer will be obtained after a 5-min rest in a seated position in the morning of the beginning and end of each intervention period.

### Daily mean concentration of coffee/cocoa-derived plasma circulating phenolic metabolites

The determination of CCDCMs will be performed in all the samples. Samples will be subjected to UHPLC-MS^n^ analysis (linear ion trap MS for identification and triple quadrupole MS for quantification purposes). Plasma samples will be extracted according to Zhang et al. [39], while urine samples will be centrifuged, diluted, and filtered. Methylxanthines, trigonelline, other pyridine metabolites, diterpenes, and phenolic metabolites will be determined as previously described [32–35]. Accurate calibration and absolute quantification will be achieved by comparison with authentic standards when commercially available or with standards previously synthesized [40, 41].

### Pharmacokinetic studies

Metabolite data will be analyzed using the WinNonlin software (Certara, LP, Princeton, NJ, USA). Pharmacokinetic parameters of each volunteer will include maximum, minimum, and average plasma concentration (C_max_, C_min_, and C_avg_), degree of fluctuation, area under the curve from 0–24 hours (AUC_0–24_), times of maximum and minimum plasma concentrations (T_max_ and T_min_), and they will be calculated for each metabolite (Fig. 3). Urinary excretion kinetics will also be estimated.

**Fig. 3 Fig3:**
[figure not shown]
Modelled pharmacokinetic profile recorded after repeated consumption of coffee along the day. *C*
_*max*_ maximum concentration, *C*
_*avg*_ average concentration, *C*
_*min*_ minimum concentration, *SD* sampling day

### Trimethylamine N-oxide

Trimethylamine N-oxide (TMAO) is a novel biomarker of cardiovascular risk produced from L-carnitine with involvement of the gut microbiota and, thus, influenced by the diet [42, 43]. It will be quantified by UHPLC-MS^n^ in baseline (0 h) plasma samples before and after each treatment. Before the analysis, TMAO-d9 will be added to samples as internal standard after which the plasma will be extracted with acidified acetonitrile as described previously [44]. Samples will be centrifuged and the supernatants collected for the UHPLC-MS^n^ analysis.

### Inflammatory markers

Some markers associated with inflammatory processes linked to the onset of atherosclerosis will be analyzed with a Bio-Plex Pro™ Human Cytokine Assays (Bio-Rad Laboratories S.r.l., Segrate, Italy). The concentrations of interferon gamma (IFN-γ), interleukin (IL)-1β, IL-2, IL-4, IL-5, IL-6, IL-7, IL-8, IL-10, IL-12 (p70), IL-13, IL-17, monocyte chemotactic protein 1 (MCP-1), and tumor necrosis factor alpha (TNF-α) will be measured by using a Bio-Plex® MAGPIX™ Multiplex Reader (Bio-Rad Laboratories). These analyses will be performed in the baseline (0 h) plasma before and after each treatment.

### Nitric oxide

Increased nitric oxide (NO) bioavailability is inversely associated with endothelial dysfunction. NO acts as an endogenous vasodilatory factor involved in the regulation of the endothelial function, maintaining an anti-inflammatory environment in the vessel [45]. Plasmatic NO, assessed as nitrate/nitrite, will be determined at the beginning and end of each intervention period using Nitrate/Nitrite Fluorometric Assay Kit (Vinci-Biochem S.r.l., Vinci, Italy).

### Blood lipids

Plasma total cholesterol, high-density lipoprotein (HDL)-cholesterol, low-density lipoprotein (LDL)-cholesterol, and triglycerides will be analyzed by standardized routine hospital protocols at the beginning and end of each intervention period.

### Fasting indices of glucose/insulin metabolism

In order to investigate the effect of the chronic coffee consumption on diabetes and insulin resistance prevention, plasma glucose and insulin concentrations will be monitored at fasting state before and after each intervention period. The analysis of glycemia will be performed by means of an automatic analyzer with a combined enzymatic-electrochemical system (YSI 2900 STAT PLUS, Yellow Springs Instruments, Yellow Springs, OH, USA). Plasma insulin concentration will be monitored by using routine blood analysis. Fasting insulin sensitivity will be determined using the quantitative insulin sensitivity check index (QUICKI) [46]. Fasting insulin secretion capacity will be evaluated as the homeostatic model assessment (HOMA) for beta cell function (HOMA-B) [47] and for insulin resistance (HOMA-IR) [48].

### DNA damage (Comet assay)

H_2_O_2_-induced DNA damage (i.e. oxidatively induced DNA damage) and formamidopyrimidine DNA glycosylase-sensitive sites of DNA (i.e. endogenous oxidative base damage) will be evaluated by the Comet assay, a procedure for the evaluation of DNA damage in all types of eukaryotic cells and tissues. DNA damage will be evaluated in PBMCs before and after each treatment, in parallel with the pharmacokinetic study in order to determine the effect of both acute and long-term consumption [49].

### DNA damage (oxidation catabolites)

DNA oxidation catabolites (8-hydroxy-2′-deoxyguanosine, 8-hydroxyguanosine, 8-nitroguanosine, guanosine-3′-5′-cyclic monophosphate, and 8-nitroguanosine-3′-5′-cyclic monophosphate) will be measured in plasma, collected before and after each treatment, by UHPLC-MS/MS, in parallel with the pharmacokinetic study in order to determine the effect of both acute and long-term consumption [50].

### Eicosanoids (oxidative stress, vascular, and inflammatory markers)

Eicosanoids are biomarkers for tracking changes in lipid peroxidation and vascular events. The eicosanoid family comprises prostaglandins, thromboxanes, and isoprostanes. These markers will be evaluated in urine before and after each treatment by UHPLC-MS/MS [51].

### Nutri-metabolomics

Urine and plasma samples at the beginning and end of each intervention period will be subjected to untargeted high-resolution-liquid chromatography mass spectrometry (HR-LC-MS/MS) metabolomics and lipidomics approaches, in order to assess potential differences between control (before) and treatment (after), as well as among the three treatments described. Metabolomics analysis and data processing will be carried out following previous works in the field [52, 53], as well as lipidomics [54]. Both works will be carried out by using a Vion Ion Mobility Quadrupole Time of Flight Mass Spectrometry (Waters, Milford, MA, USA). This explorative investigation will be applied as a complementary assay to generate a comprehensive picture of the impact of coffee and the cocoa-based product containing coffee on human health.

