**Methods:**

A three-arm, crossover, randomized trial will be conducted. Twenty-one volunteers will be randomly assigned to consume three treatments in a random order for 1 month: 1 cup of espresso coffee/day, 3 cups of espresso coffee/day, and 1 cup of espresso coffee plus 2 cocoa-based products containing coffee twice per day. The last day of each treatment, blood and urine samples will be collected at specific time points, up to 24 hours following the consumption of the first product. At the end of each treatment the same protocol will be repeated, switching the allocation group. Besides the bioavailability of the coffee/cocoa bioactive compounds, the effect of the coffee/cocoa consumption on several cardiometabolic risk factors (anthropometric measures, blood pressure, inflammatory markers, trimethylamine N-oxide, nitric oxide, blood lipids, fasting indices of glucose/insulin metabolism, DNA damage, eicosanoids, and nutri-metabolomics) will be investigated.

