**Fig. 2 Fig2:**
[figure not shown]
SPIRIT figure: summarizes the allocation, interventions, and outcomes of the study

Subjects will be assigned to consume the following treatments in a random order for one month (including the sampling day -the last day of each intervention period-):one cup of espresso coffee/day (“low consumers”) at 9.00 AM;three cups of espresso coffee/day (“high consumers”) at 9.00 AM, 12.00 PM, and 3.00 PM;one cup of espresso coffee at 9.00 AM and two cocoa-based products containing coffee two times per day, at 12.00 PM and 3.00 PM. This group will be named “medium consumers”, in view of the caffeine content of the cocoa-based product containing coffee.

Minimal recommendations to avoid other sources of coffee/cocoa-related phytochemicals besides those introduced through the assigned treatment, and to standardize the time of coffee consumption, will be provided for the 2 days prior to each sampling day and on the sampling day. Dinner timing and composition will also be standardized the day before the sampling day. Only water could be drunk during the night. In the morning of the sampling day, the subjects will attend a clinic where fasting baseline blood and urine samples will be collected. Then, low and high consumers will drink one or three cups of espresso coffee, respectively (without sugar, sweeteners, and milk for the first coffee; with 5 g of sugar for the last two coffees), while medium consumers will drink a cup of espresso coffee and two cocoa-based products containing coffee twice during the course of the day, following the above mentioned timing. After ingestion of the first coffee together with a polyphenol-free breakfast (a sponge milky cake), blood and urine samples will be collected at selected time points over the ensuing 24-h time points (Fig. 1). Five hours after the consumption of the first coffee, participants will receive a standardized mixed meal (ham and cheese sandwich) free of coffee/cocoa-related phytochemicals. Water will be available ad libitum. Twenty-four hours after receiving the treatment, blood and urine samples will also be taken in order to assess return to baseline. In addition, anthropometric characteristics and blood pressure will be measured.

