### Inclusion and exclusion criteria

Inclusion criteria will include being adult, healthy, of normal weight [body mass index (BMI) 18–25], and regular consumers of one to five cups of coffee per day. Exclusion criteria will include clinical diagnosis for metabolic, renal or digestive disorders, regular consumption of medication, antibiotic therapy taken within the last 3 months, intense physical activity, pregnancy or lactation, regular intake of coffee exceeding five coffees per day, and very high consumption of coffee/cocoa-related phytochemicals. These criteria are set in order to avoid likely confounding factors [36].

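### The start-of-period sample is labelled a control but is not one, so a within-arm before-after test does not isolate a treatment effect

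*Protocol article*

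**What the plan says.** The Nutri-metabolomics section of the protocol article takes urine and plasma at the start and end of each period "in order to assess potential differences between control (before) and treatment (after), as well as among the three treatments described". That names two comparisons, and the first calls the start-of-period sample a control.

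Other sections use the same sampling frame:

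- TMAO is measured in "baseline (0 h) plasma samples before and after each treatment". Cytokines and eicosanoids are also taken before and after each treatment.
- Anthropometry, blood pressure, nitric oxide and blood lipids are taken at the beginning and end of each period.
- Fasting glucose and insulin are taken before and after each period, and the stated purpose is to study the effect of chronic coffee consumption.
- Both DNA-damage sections sample before and after each treatment and give acute and long-term effects as the purpose.

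On the design, the Abstract says: "At the end of each treatment the same protocol will be repeated, switching the allocation group". Under Protocol and study design, "Subjects will be assigned to consume the following treatments in a random order for one month", with the sampling day as the last day. All three arms contain espresso. Entrants are "regular consumers of one to five cups of coffee per day". The text gives no interval between periods, and Fig. 1, which shows the design, is not available to this review.

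The statistical section names repeated-measures general linear models or the Friedman test. It does not say whether arms are compared on end-of-period values or on within-period changes.

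**The concern.** A control sample should show the volunteer without the treatment under study. Here no sample does. The first start-of-period sample shows whatever the volunteer usually drinks, which may be more or less than the assigned arm. If periods follow each other directly, the second and third come after a month on one of the other arms. That is two of every three start-of-period samples (42 of 63 with 21 volunteers).

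A before-after difference within an arm then mixes the arm's effect with habitual intake, the preceding arm and any time trend. Reported as the effect of that coffee level, it could have the wrong size or even the wrong sign. The outcomes concerned are the secondary cardiometabolic markers, which serve objective (ii), and the metabolomic and lipidomic profiles.

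**Working it through.** The plan gives no figure on this point to reproduce. The check asks what a before-after change measures under the stated design.

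**Inputs.** Three arms, three periods, 21 volunteers (Abstract, Methods). About 60 mg caffeine per espresso and about 30 mg per two cocoa products (Testing materials). The daily scale is therefore low 60, medium 60 + 30 + 30 = 120, high 3 × 60 = 180. It serves only as a convenient scale for an effect proportional to dose. Habitual intake of one to five cups is b = 60 to 300 on the same scale, assuming a habitual cup equals a study cup.

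**Model (assumed).** The end-of-period value reflects the current arm, t. The start-of-period value is b in period 1 and b + λ(previous arm − b) afterwards. λ = 0 means full return to habit; λ = 1 means the previous arm's effect persists fully.

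**Within-arm change.** With all six orders equally frequent and λ = 1, each arm is preceded one third of the time by habit and one third by each other arm:

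mean change in arm i = t_i − (b + t_j + t_k)/3

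For b = 180, low: 60 − (180 + 120 + 180)/3 = −100.

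| Habit b | Low | Medium | High |
|---|---|---|---|
| 60 | −60 | +20 | +100 |
| 180 | −100 | −20 | +60 |
| 300 | −140 | −60 | +20 |

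The medium arm's change switches sign with habitual intake alone. At λ = 0 the change is t_i − b: for b = 180 it is −120, −60 and 0, so the high arm appears to do nothing.

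**Between-arm contrast of changes, if used.** Subtracting two arms removes b:

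contrast = (1 + λ/3)(t_i − t_j)

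This gives 1.00, 1.17 and 1.33 times the truth at λ = 0, 0.5 and 1. A simulation with 21 volunteers, full persistence and a true high-minus-low difference of 1.00 gave 1.33 for changes and 1.00 for end-of-period values.

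**One cyclic Latin square** (L-M-H, M-H-L, H-L-M), λ = 1:

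- High − low: 120 + (2/3)(180 − 120) = 160, ratio 160/120 = 1.33.
- Medium − low: 60 + (2/3)(180 − 60) = 140, ratio 140/60 = 2.33.
- High − medium: 60 + (2/3)(60 − 120) = 20, ratio 20/60 = 0.33.

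The reverse square exchanges the last two ratios.

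**Precision.** Take independent within-volunteer errors of variance σ². An end-value contrast has variance 2σ² per volunteer. With a fresh start-of-period sample, the change contrast has 4σ², so the SD ratio is √2 = 1.41 (simulated 0.216/0.154 = 1.40). If one specimen is both the end of one period and the start of the next, the variance is 6σ² for arms in adjacent periods (two thirds of cases) and 4σ² otherwise. The average is 16σ²/3 and the ratio √(8/3) = 1.63 (simulated 0.254/0.157 = 1.62).

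**The case against.** The word control appears only under Nutri-metabolomics, which the article calls explorative and complementary. The same sentence lists comparison among the three treatments separately, and the statistical section's models fit that comparison on end-of-period values. Objective (ii) is itself about levels of consumption, a between-arm question. Most marker sections only give sampling times. The choice between end value and change is often left to an analysis plan, and a washout may be shown in Fig. 1.

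Much of this stands, and it rules out several stronger readings that a reader might infer.

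- **That arm differences will be overstated by a third.** This needs change scores, full persistence and six equally frequent orders. The article fixes none of them, and 21/6 = 3.5, so exact balance over six orders is impossible at that number. With a single three-sequence square some contrasts shrink.
- **That there is certainly no washout.** The visible text supports only that none is described.
- **That diet preparation also separates before from after.** The recommendations "will be provided for the 2 days prior to each sampling day and on the sampling day", but the article does not say that the first visit lacked such preparation. That is inference from silence.
- **That objective (ii) will be answered with wrong numbers.** Comparing end-of-period values is compatible with the text.

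The objection does not remove the stated comparison. A washout in Fig. 1 would not make habitual coffee a control in period 1, and it would not give a within-arm test a concurrent comparator against time trends. The glucose/insulin and DNA-damage sections also attach an effect-of-consumption purpose to before/after sampling, so the problem is not confined to one word in one section.

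**Conclusion.** The point holds as a mislabelled comparison. The start-of-period sample is not a control, and a within-arm before-after P value does not isolate the effect of a coffee level. This follows from the entry criterion and from every arm containing coffee, whatever Fig. 1 shows. That the samples in periods 2 and 3 follow another arm is probable rather than established.

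The bias in between-arm contrasts is conditional on comparing changes: 0 to +33% with balanced orders depending on persistence, and ratios from 0.33 to 2.33 with one cyclic square, full persistence and equally spaced effects. The loss of precision, 1.41 or 1.63 times the SD, assumes independent errors of equal variance; the 1.41 does not depend on washout. End-of-period contrasts are unbiased in this model because it assumes that nothing from the previous arm remains after a month on the next.

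The primary endpoint comes from the sampling day at the end of each period and is not affected. The consequence is limited to what the secondary and exploratory analyses can claim.

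**What to change.** For the cardiometabolic, metabolomic and lipidomic outcomes:

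1. Compare the three arms within volunteer on end-of-period fasting values, in a model with treatment and period terms. A variable sent to the Friedman test should also enter as its three end-of-period values, noting that this test has no period term.
2. Use the sample before period 1 only as a volunteer-level descriptor.
3. Drop the control label and make any before-after comparison descriptive, without a P value presented as an effect of coffee. Align the purpose statements in the glucose/insulin and DNA-damage sections.
4. Word conclusions as differences between consumption levels, since no coffee-free condition exists.
5. State the interval between periods in the text, so that readers can judge what the later start-of-period samples represent.

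The cost is analysis wording only, with no new samples or visits. What is given up is the formal within-arm before-after test.

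### The start-of-period sample is labelled a control although, on the text shown, volunteers are already drinking coffee, so a before-after change measures a switch from prior intake

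*Protocol article*

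**What the plan says.** All places are in the protocol article.

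- **Nutri-metabolomics.** Urine and plasma from the start and end of each period are analysed "in order to assess potential differences between control (before) and treatment (after), as well as among the three treatments described". The start sample is thus named as a comparator, and the before-after contrast is listed separately from the contrast among arms.
- **DNA damage (Comet assay).** Damage is measured "before and after each treatment, in parallel with the pharmacokinetic study in order to determine the effect of both acute and long-term consumption". The section on oxidation catabolites has the same scheme.
- **Fasting indices of glucose/insulin metabolism.** Glucose and insulin are taken before and after each period, with the stated purpose of studying chronic coffee consumption.
- **Other marker sections** (anthropometry, blood pressure, TMAO, cytokines, nitric oxide, lipids, eicosanoids). These give before/after or beginning/end sampling times and name no contrast.
- **Inclusion and exclusion criteria.** Entrants are "regular consumers of one to five cups of coffee per day".
- **Abstract, Methods.** "At the end of each treatment the same protocol will be repeated, switching the allocation group".
- **Protocol and study design.** Each arm lasts "one month (including the sampling day -the last day of each intervention period". Advice to avoid other sources of the phytochemicals "will be provided for the 2 days prior to each sampling day and on the sampling day". It concerns sources besides the assigned treatment and applies at the end of a period.
- **Sample size calculation, randomization and statistical analysis.** Repeated-measures linear models or the Friedman test, each with post hoc comparisons, are planned. The section does not say whether changes or end values are the response.

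**The concern.** A before-after contrast within an arm isolates that arm's effect only if the before state is a stable reference without the exposure. Here the text points the other way. In period 1 the before sample reflects habitual coffee. In periods 2 and 3 it reflects the previous arm if periods are contiguous, or habitual coffee again if there is a gap without abstinence. No text describes a coffee-free interval.

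The before-after change is then this arm minus whatever was drunk before. It depends on habit and on the order of arms, neither of which belongs to the arm. A reader of the metabolomics results, or of long-term results for glucose, insulin or DNA damage, could take a change in the low arm for an effect of drinking one cup a day when it mostly reflects a reduction in intake.

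**Working it through.** The plan gives no figure for this contrast, so there is none to reproduce. The check uses the plan's doses.

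**Inputs from the protocol article**
- Caffeine: about 60 mg per cup and about 30 mg per two cocoa products (Testing materials and phytochemical composition).
- Low arm: "one cup of espresso coffee/day (“low consumers”) at 9.00 AM" = 60 mg/day. Medium arm: one cup plus two products twice a day = 60 + 2 × 30 = 120 mg/day. High arm: three cups = 180 mg/day.
- Habitual intake at entry: 1 to 5 cups = 60 to 300 mg/day at the same 60 mg per cup.

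**Assumptions**
- Habitual mean of 3 cups (180 mg/day), with the range 1 to 5 shown below.
- Six orders equally weighted. With 21 volunteers this can only be approximate (21/6 = 3.5).
- Contiguous periods for step 2.
- Caffeine as a proxy for exposure.

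**Step 1: change by preceding state** (arm minus preceding intake, mg/day)

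| Arm | Period 1, habit 1/2/3/4/5 cups | Periods 2-3, by previous arm |
|---|---|---|
| Low | 0 / -60 / -120 / -180 / -240 | after medium -60; after high -120 |
| Medium | +60 / 0 / -60 / -120 / -180 | after low +60; after high -60 |
| High | +120 / +60 / 0 / -60 / -120 | after low +120; after medium +60 |

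The low arm never raises exposure above the preceding state.

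**Step 2: mean change with contiguous periods.** Over six orders each arm comes first in a third, and follows each of the other two arms in a third. Mean change = arm dose - (habit + the two other arms)/3.
- Low: 60 - (180 + 120 + 180)/3 = 60 - 160 = **-100**
- Medium: 120 - (180 + 60 + 180)/3 = 120 - 140 = **-20**
- High: 180 - (180 + 60 + 120)/3 = 180 - 120 = **+60**

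Against no coffee the arms supply +60, +120 and +180. As the habitual mean goes from 1 to 5 cups, the means run from -60 to -140 (low), +20 to -60 (medium) and +100 to +20 (high).

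**Step 3: a gap on habitual coffee instead.** Every before state is then 180 mg/day, and the changes are 60 - 180 = -120, 120 - 180 = -60 and 180 - 180 = 0. The between-arm differences are undistorted, but the before sample is still on coffee.

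**Step 4: a coffee-free interval before every period.** The changes would be about +60, +120 and +180, and the control label would be fair.

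**Step 5: if change scores were compared between arms, periods contiguous.** High minus low = 60 - (-100) = 160, against a true 180 - 60 = 120. The ratio is 160/120 = 4/3, and habitual intake cancels. It arises because an arm never follows itself.

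**Step 6: end-of-period values compared within volunteer.** High - low = 120, high - medium = 60 and medium - low = 60 mg/day, whatever the habitual intake, provided nothing carries over beyond the month.

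**The case against.** The case against has real force.

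- **The label is local.** It occurs only in the metabolomics section, which describes itself as explorative and complementary, and the same sentence also plans the comparison among arms. A reader might infer that the whole secondary analysis rests on before-after changes. The documents do not support that. Most marker sections give sampling times only, and the statistical section never mentions change scores. The objective on cardiometabolic risk factors concerns different levels of consumption, which is a between-arm question. This stands. The comparator in the metabolomics section, and the link to chronic or long-term consumption in the glucose/insulin and DNA-damage sections, are nevertheless in the text.
- **Fig. 1 is not shown.** A coffee-free interval there would remove the problem (step 4). Contiguity rests on one sentence of the abstract, and measuring weight and blood pressure at both ends of each period makes some gap plausible. This stands, so the point is conditional. A gap on habitual coffee would not be enough.
- **Wrong sign.** A reader might infer that results will point the wrong way. If intake falls from three cups to one, a fall in a coffee-raised marker has the correct sign for that switch. It misleads only if read as an effect against no coffee, an estimand the protocol does not state.
- **Marker-level size.** The article itself describes a U-shaped relation for cardiovascular disease, and the cocoa products also bring flavan-3-ols and theobromine. A simulation with 21 volunteers, contiguous periods and a linear effect shows how far an assumption would drive the answer. The low arm is significantly negative in about 8% of trials at 0.1 within-person SD per cup and about 70% at 0.5. The documents give no basis for choosing between them, so no error rate belongs in the finding.

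**Conclusion.** The concern holds in a limited, conditional form. Unless Fig. 1 shows a coffee-free interval before each period, the start-of-period sample is not a control, and the before-after change estimates a switch from prior intake. Under the assumptions above, mean exposure changes by about -100, -20 and +60 mg caffeine/day in the low, medium and high arms, against +60, +120 and +180 versus no coffee. The size in any marker is unknown.

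The inflation of the high-low contrast from 120 to 160 mg/day applies only if periods are contiguous and change scores are compared between arms, and the article states neither outright. The primary endpoint, the daily mean plasma concentration of phenolic metabolites, is not touched. Nor is the randomised comparison of end-of-period values.

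**What to change.** - In Nutri-metabolomics, remove the control label and do not read the before-after change as a treatment effect.
- For metabolomics and the cardiometabolic markers, base long-term conclusions on the within-volunteer comparison of end-of-period values (0 h on the sampling day) among the three arms. State this response variable in the statistical section.
- Report before-after changes, if at all, as descriptive changes from prior intake.
- State that no arm is compared with no coffee.
- If Fig. 1 does contain a coffee-free interval before each period, say so in the text. The label could then stay.

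**Cost.** Wording only. The samples and visits are already planned, and so is the among-arm comparison. The downside is that the trial gives up claims of improvement from baseline.
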